#### Blinding and clinical review of study data

All data collected for the study, except calculated MRI biomarkers and ICG measurements, are acquired as part of the routine workup and will therefore be available to the clinical care team through the participant’s medical records. ICG liver function measurements will be made available to the clinical care team to inform management as appropriate. MRI scans will be reviewed by the radiology department and any unusual findings will be flagged up to the clinical care team. The research fellows working on MRI data processing and statistical analysis will be blinded to the clinical history of the participant and other function tests.

#### Long-term data storage

Study documents with identifiable data will be retained for 10 years in line with the MRC Good Research Practice guidelines (Medical Research Council 2012) and then destroyed using the hospital’s confidential waste management service. During this ten-year period data will be stored securely on the hospital’s premises and secure electronic systems. Access to the data during this period will only be available with the consent of one of the study’s clinical supervisors.

All excel sheets with anonymised study data will be transferred to a long-term data repository where they will be maintained for a minimum of 25 years. Source data for MRI and ICG will be retained indefinitely in a dedicated imaging data management system hosted by the University to enable secondary research, educational use, and data sharing.

#### Withdrawal of participants

If a participant decides to withdraw their consent to inclusion in the study at any point then no further data regarding their care will be collected. Should the participant wish, data collected up until withdrawal of consent will be destroyed. Participants who lose their capacity to consent will be treated in the same manner as if they had withdrawn consent. Previously collected data will not be destroyed. If a participant is unable to complete their MRI study for any reason they will automatically be withdrawn from the study. Data collected until the point of withdrawal will be retained, unless the participant requests they are deleted,

#### Blood samples

Blood samples taken after ICG injection at the baseline visit will be processed in the LICAMM laboratories. Whole blood and blood plasma will be stored in a secure sample storage facility within LICAMM with access limited to LICAMM staff. Samples will be stored in a freezer and will only be accessed by members of the research team. ICG concentrations will be measured in batch after finalizing recruitment. The remaining samples will be stored for a maximum of 5 years to measure metabolomics data for secondary research. Precise use will be based on future research priorities. After 5 years any remaining samples will be destroyed according to standard LICAMM procedure for sample disposal.

### Sample size considerations

#### Audit

Sample size calculation was informed by an audit of the preceding year. Between October 2016 and October 2017, a total of 165 patients who met the inclusion criteria underwent surgery at St James’s hospital. 15% of these patients underwent PVE. Patients undergoing major liver resection had a rate of PHLF equal to 9%, although the rate of those requiring medical intervention as a result of their PHLF was only 3.6%. Of the eligible patients, 67% had an MRI in Leeds after the MDT, and for a further 7% the MDT requested a local MRI.

For practical and funding reasons the maximum duration of patient recruitment in HEPARIM was set at 2 years. Based on experience in a pilot study [22], a 50% recruitment rate was assumed in patients that do not require an additional MRI visit for research purposes. A 25% recruitment rate was assumed in primary surgery patients that need an additional MRI, and in PVE/ALPPS patients.

With these assumptions the maximum number of participants over the 2 years is 134, including 122 into the primary surgery arm and 12 into the PVE/ALPPS arm. The pilot study also demonstrated that 18% of patients recruited into the study ultimately did not undergo surgery. Hence only 82% of the 122 recruited patients in the surgery arm will feed into the primary objective, or a total of 112 including those in the PVE/ALPPS arm.

#### Power calculation

The power calculation was informed by pilot data in 29 cases, without ICG measurement [22]. The following assumptions were made: (1) patient population values of FLR-GC follow a log-normal distribution; (2) ICG-C = 10 x FLR-GC + e, with an error variance that reflects uncertainty in this relationship. The factor 10 encodes the fact that ICG extraction fractions are an order of magnitude higher than for Gadoxetate; (3) error variance is proportional to true FLR-GC, which invokes heteroscedasticity, as observed for the pilot data.

The impact of study size was assessed by simulating a hypothetical population of 1 million patients and evaluating model robustness to estimate the model beta coefficient of FLR-GC in relation to ICG-C. The relationship between FLR-GC and ICG-C values is modelled for different error variances ranging from very low precision (4 times the variance of FLR-GC) to good precision (one quarter the variance of FLR-GC). 10 k samples of 120 patients are drawn with replacement for each of the three error variances, generating empirical distributions of the parameters.

Figure 2 shows an example with error variance reflecting low precision. A plot of the model standard errors is also shown and reveals how optimal precision is around the largest cluster of data points towards the lower range of FLR-GC values (1.3 mL/min/kg). At this lowest precision, the 95% confidence interval for the model beta coefficient ranges from 9.12 to 10.88 with a median of 10.01 – very close to the exact value of 10. The half-width of the 95% CI is 8.8% of the exact value, showing that the sample size is sufficient to obtain reliable beta coefficients even at the poorest precision simulated.

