##### Questionnaires

An initial dataset will be captured incorporating the participant’s medical history and up-to-date investigations. This will be obtained through a combination of interview, review of paper notes and review of the electronic medical record. An MRI safety screening form will be administered. If a contraindication to MRI is found at this point, the visit will be cancelled, and the participant will be excluded from the study. An ICG safety questionnaire will be used to exclude participants with contraindications to ICG use. Participants excluded from ICG testing at this point will not be excluded from the study as other measures of liver function will still be available for analysis of secondary outcomes.

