#### In-patient follow-up

Once the participant’s surgery is complete, data obtained as part of the participant’s standard intra and post-operative care will be collected. This includes any blood tests during admission, the characteristics of the operation, complications and length of stay. Pathology results will be collected once reported. The ICG test with the finger-clip device will be repeated postoperatively at bedside to determine a reference value for postoperative liver function. This will be performed on day 1 post-surgery if feasible. A range of biochemical measures will be used to calculate postoperative liver function using the post-operative data set.

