### Study procedures (PVE/ALPPS arm)

Participants requiring PVE/ALPPS will be recruited in the same way as participants in the resection arm. They will attend the same baseline visit and the routine clinic visit. Participants may decline the PVE/ALPPS at this point, or the clinician may decide it is inappropriate at the clinic appointment. If this occurs and the participant proceeds to surgery, they will remain in the study. If they do not proceed to surgery their data will be used to address the secondary objectives.

A participant who does proceed to PVE/ALPPS will attend the hospital for a routine CT scan after the first stage, and a second research visit will be scheduled at that point. This visit will proceed in the same manner as the baseline visit. They will be re-discussed in the MDT and come for a preoperative clinic appointment. Participants may be deemed ineligible for surgery, or make the decision not to proceed with surgery, in which case their data already collected can feed into the secondary objectives. If they do proceed to surgery, the same intra-operative and post-operative data will be taken as for the resection arm.

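### The precision simulation uses samples of 120, but the plan's own accounting leaves only 112 participants for the primary objective

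*Protocol article*

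**What the plan says.** The Audit section of the protocol article starts from one year of local activity, in which "a total of 165 patients who met the inclusion criteria underwent surgery at St James’s hospital". Of these, "15% of these patients underwent PVE". On imaging, "67% had an MRI in Leeds after the MDT, and for a further 7% the MDT requested a local MRI". With assumed recruitment rates of 50% (no extra research MRI needed) and 25% (extra MRI needed, or PVE/ALPPS), it arrives at a two-year maximum of 134 recruits: 122 for primary surgery and 12 for PVE/ALPPS. It then takes an 18% failure to reach surgery from the pilot study and concludes: "Hence only 82% of the 122 recruited patients in the surgery arm will feed into the primary objective, or a total of 112", counting the PVE/ALPPS arm.

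The Power calculation section does not carry the 112 forward. It says that "10 k samples of 120 patients are drawn with replacement for each of the three error variances". At the lowest precision it reports an interval of 9.12 to 10.88 for a true slope of 10, a half-width of 8.8%, and concludes that the sample size is adequate.

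For the PVE/ALPPS arm, the Study procedures section says of the period after the second research visit: "Participants may be deemed ineligible for surgery, or make the decision not to proceed with surgery". It describes a similar exit at the earlier clinic visit.

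**The concern.** Two adjacent sections use different numbers for the same quantity. The simulation is meant to show how precisely the slope relating FLR-GC to post-operative ICG clearance can be estimated, so it should be run at the number of participants expected to supply that pair of measurements. By the article's own count this is 112. Recruitment was capped for practical and funding reasons, so the simulation is the only statistical justification of the sample size that the article gives. Its result should describe the sample that the plan expects.

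A second, smaller inconsistency lies inside the 112. The loss before surgery is deducted from one arm and not from the other, and the article's own text makes some loss in the second arm plausible.

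**Working it through.** **Inputs (Audit section).** 165 eligible patients per year for 2 years; 15% PVE; 67% + 7% = 74% needing no extra MRI; recruitment rates 50% and 25%; 18% not reaching surgery.

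**1. Reproduce the recruitment target.**
- Eligible: 165 × 2 = 330, of which 330 × 0.85 = 280.5 primary surgery and 330 × 0.15 = 49.5 PVE.
- Primary surgery: 280.5 × (0.74 × 0.50 + 0.26 × 0.25) = 280.5 × 0.435 = 122.0.
- PVE/ALPPS: 49.5 × 0.25 = 12.4.
- Total: 134.4, which agrees with the stated 134 = 122 + 12.

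**2. Reproduce the number for the primary objective.**
- 0.82 × 122 = 100.04, and 100.04 + 12 = 112.04, the stated 112. It is obtained by keeping all 12 PVE/ALPPS recruits.
- With the same 18% loss in both arms: 0.82 × 134 = 109.9, about 110.

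**3. Compare with the simulated number.**
- 120/112 = 1.07 and 120/110 = 1.09, so the simulated sample is 7% or 9% too large.
- Obtaining 120 after an 18% loss in both arms would need 120/0.82 = 146.3, so 147 recruits. With no loss among the 12 PVE/ALPPS recruits it would need (120 − 12)/0.82 + 12 = 143.7, so 144. Both exceed the stated maximum of 134.

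**4. Effect on precision.**
- Stated half-width: (10.88 − 9.12)/2 = 0.88, or 8.8% of 10. This agrees with the article.
- Scaling by √(120/n):

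| n | √(120/n) | Half-width | % of 10 | Approximate interval around 10 |
|---|---|---|---|---|
| 120 (as simulated) | 1.000 | 0.880 | 8.8% | 9.12 to 10.88 |
| 112 (plan's own count) | 1.035 | 0.911 | 9.1% | 9.09 to 10.91 |
| 110 (18% loss in both arms) | 1.044 | 0.919 | 9.2% | 9.08 to 10.92 |

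**5. Check of the scaling.** The article does not give the parameters of its log-normal distribution, so its interval cannot be reproduced exactly. A Monte Carlo check used 10,000 samples per n, a median FLR-GC of 1.3, assumed coefficients of variation from 0.3 to 1.1, and two forms of heteroscedasticity. Across ten settings the half-width at 120 ranged from about 0.4 to 1.3, so absolute values from this check are not usable. The widening from 120 to 112 was about 1.5% to 6% in nine settings and nil in one, within simulation noise. This is in line with the 3.5% from root-n scaling.

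**The case against.** **The effect is trivial.** The half-width moves by 0.3 to 0.4 percentage points, and the article sets no precision threshold that 9.1% or 9.2% would fail. This stands. It limits the point to a correction of stated figures, and a reader who inferred that the sample is too small would go beyond what the arithmetic shows.

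**The 110 is not a correction.** The 18% comes from a pilot in 29 patients with colorectal liver metastases, and the article gives no rate for the PVE/ALPPS pathway. That stands too: 110 is a sensitivity value, and only 2 patients are at issue. One could add that the audit counted patients who had been operated on, so the PVE share is already conditional on surgery. But the primary surgery arm comes from the same audited patients and still has 18% deducted, so this does not explain why the two arms are treated differently.

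**Further losses might be inferred.** The article says that "Participants excluded from ICG testing at this point will not be excluded from the study", and of the post-operative ICG test that "This will be performed on day 1 post-surgery if feasible". It also withdraws participants who cannot complete the MRI. A reader might conclude that the evaluable number is well below 110. The article gives no rate for any of these, the feasibility condition may qualify only the day and not whether the test is done, and an allowance for missing tests or a definition of the analysis set is commonly left to the full protocol or SAP. No figure can be attached to them here. The exclusion criteria list ICG contraindications while the Questionnaires section retains such participants. That is a separate conflict to reconcile.

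**The recruitment rule.** A reader might infer that recruits without a primary endpoint use up the 134. The Timing section can be read as counting only those who complete imaging, surgery and follow-up, so this is not established. That reading does not rescue the 120 either, because the Audit section itself reduces 134 recruits to 112.

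**Conclusion.** The mismatch is real and needs no outside assumption: 120 was simulated, 112 are expected, and the article gives no reason for the difference. The published interval and half-width are slightly too favourable for the expected sample. The half-width is about 9.1% at 112, assuming root-n scaling from the article's own result. The full retention of the PVE/ALPPS arm is a lesser inconsistency. If 18% is assumed to be lost there as well, about 110 remain and the half-width is about 9.2%. The conclusion that the sample gives reliable slope estimates is not overturned by this point.

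**What to change.** - Rerun the simulation at 112, with 110 as a sensitivity value, and restate the 95% interval and half-width for those sizes.
- In the Audit section, either apply the loss before surgery to both arms or state that none is assumed in the PVE/ALPPS arm, and why.

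The cost is one rerun of an existing simulation and a few changed sentences. No extra patients are needed, and the stated precision becomes marginally less favourable.

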**Fig. 2 Fig2:**
[figure not shown]
Predicted ICG-C (top) and error in the predicted ICG-C (bottom) for the lowest precision simulated

## Discussion

Despite recent changes in surgical practice with increased appetite towards parenchymal preserving surgery for superficial liver tumours, patients with multiple, deep or perivascular lesions still require major resectional surgery and are not amenable to simple metastasectomy. For these patients PHLF remains a major concern, the risk of which can potentially be reduced with a reliable and widely available prediction of post-operative function. Such a test could also help guide patient selection for PVE, two stage surgery and ALLPS and determine which patients do in fact need portal embolisation and which patients can safely proceed straight to surgery. Once selected for PVE, two stage surgery or ALPPS, a partial liver function test may improve decisions on the optimal time interval between vascular intervention and surgery. This can potentially reduce the risk of further tumour invasion or growth in the waiting period between the two surgical stages.

Currently available liver function tests are limited either by their inability to assess regional segmental liver function directly or are not widely available. The HEPARIM trial will examine the ability of a novel MRI-based technique to accurately measure FLR function and predict PHLF using FLR-GC as an index of direct regional hepatocyte function. Being an MRI modality, it can be embedded in the current pre-operative diagnostic algorithm without the need for additional procedures in most patients and in a cost-effective manner. Assuming a positive outcome, HEPARIM will produce strong hypotheses that can inform improved management strategies and future clinical trials to test their safety and efficacy. Potentially, this could include extending the indication for surgery in a subgroup of liver cancer patients that are currently considered inoperable due to the high risk of PHLF, but who have a poor prognosis without surgery.

## Data Availability

The data sharing policy for HEPARIM is specified in the Data Management Plan of the funding application and in line with MRC requirements and guidelines. All data will be made available for secondary research by other internal or external investigators, and for educational or commercial purposes. Suitability for sharing: All anonymised data are suitable for sharing. One reason for sharing is to allow independent verification by other researchers, or to develop novel data processing and modeling methods that produce novel biomarkers or more accurate values. The data will also be useful for validating implementations in other centres, or as part of a future quality assurance process. Discovery by potential users of the research data: A project website will be set up which will contain basic information about the project, investigators, results and news, access to software and training materials, and also examples of the data and modalities for data sharing. Governance of access: The decision process for supplying the data will follow the data sharing request workflow as specified on p11 in the MRC policy and guidance on Sharing of Research data. For this study, requests will be approved following model 2. The study team’s exclusive use of the data: The study team’s exclusive use of the data will be restricted to the duration of the study. Restrictions or delays to sharing: The patient consent form contains a section explaining the use of the data for the research project and future exploitation by third parties, and the conditions under which they will be released. Patients will only be enrolled in the study if they consent to these modalities. There are no restrictions or delays to sharing expected. Regulation of responsibilities of users: Users will need to sign a data sharing agreement. This will lay out user responsibilities such as checking for internal review board approval, making no attempts to establish the identity of the subjects, adhering to redistribution rights and licensing, acknowledging the funding body and authors in future publications.

## Abbreviations

AEs: All adverse events
ALPPS: Associating liver partition and portal vein ligation for staged hepatectomy
CCA: Cholangiocarcinoma
CRC: Colorectal cancer
CT: Computerized tomography
DGE- MRI: Dynamic gadoextate enhanced magnetic resonance imaging
FLR: Future liver remnant
GC: Gadoxetate clearance
HPB: Hepatobiliary
HCC: Hepatocellular carcinoma
ICD: Implantable cardiac device
ICG: Indocyanine green
MDT: Multi-disciplinary team
MRI: Magnetic resonance imaging
PHLF: Post hepatectomy liver failure
PPM: Permanent pacemaker
PVE: Portal vein embolisation
R15: Retention rate at 15 min
SAEs: Serious adverse events
WH: Whole liver
